## **4.2. Handling of missing data**

Missing data will be handled by appropriate techniques, such as multiple imputation or mixed effect models. To reduce missings, the scientific importance of conscientious participation and complete filling in of questionnaires will be explained to patients. Using digital assessment tools will further reduce missing data. Study personnel will monitor the completion of measures and will identify problems as early as possible.

### **DiLCoS Substudy**

Participation in the intervention will be monitored by study personnel. If participants do not visit the smartphone application for more than two days, they will be contacted via the applications' chat function. If there is no activity for an additional two-day period, they will be contacted via phone to solve potential problems. Participants who attended less than 50% of the intervention weeks will be excluded from completer analyses.

## **5 REGULATORY ASPECTS AND SAFETY**

### **5.1 Local regulations / Declaration of Helsinki**

This research project will be conducted in accordance with this study protocol, the Declaration of Helsinki (World Medical Association, 2013), the principles of Good Clinical Practice, the Human Research Act (HRA; The Swiss Federal Council), and the Human Research Ordinance (HRO; Federal Office of Public Health, 2022) as well as other locally relevant regulations. Both the project leader and the sponsor acknowledge their responsibilities.

### **5.2 Notification of safety and protective measures (HRA Art. 15, HRO Art. 20)**

If, during the research project, circumstances arise which could jeopardize the safety or health of the participants or lead to a disproportionate relationship between the risks or burdens and the benefits, all the measures required to ensure protection are to be taken without delay.

The project leader and the sponsor are promptly notified (within 24 hours) if immediate safety and protective measures have to be taken during the conduct of the research project. The Ethics Committee will be notified via BASEC of these measures and of the circumstances necessitating them within 7 days.

### **5.3 Serious events (HRO Art. 21)**

If a serious event occurs, the research project will be interrupted and the Ethics Committee notified of the circumstances via BASEC within 7 days according to HRO Art. 21.

Patients will be recruited from an outpatient setting; participating in the proposed study does not influence standard care. We do not expect any SAEs to occur as a consequence of the tests administered for this study in addition to standard care.

### **5.4 Procedure for investigations involving radiation sources**

Not applicable.

### **5.5 Amendments**

Substantial changes to the project set-up, the protocol, and relevant project documents will be submitted to the Ethics Committee for approval according to HRO Art. 18 before implementation. Exceptions are measures that have to be taken immediately in order to protect the participants.

### **5.6 End of project**

Upon project completion or discontinuation, the Ethics Committee will be notified within 90 days. All biological materials and health-related data are encoded upon termination of data analysis (also refer to section 7.4). If the respective consent is given (see consent form), the biological material (blood) will be stored in the biobank at the UHB and can be used in follow-up/additional projects. All other samples will be destroyed.

### **5.7 Insurance**

In the event of project-related damage or injuries, the Sponsor will be liable (covered by the liability insurance of USB), except for damages that are only slight and temporary; and for which the

---

 A serious event is defined as any adverse event where it cannot be excluded, that the event is attributable to the sampling of biological material or the collection of health-related personal data, and which:

- a. requires inpatient treatment not envisaged in the protocol or extends a current hospital stay;
- b. results in permanent or significant incapacity or disability; or
- c. is life-threatening or results in death.

extent of the damage is no greater than would be expected in the current state of scientific knowledge (Art. 12 HRO).

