### **DiLCoS Substudy**

The intervention substudy is designed as a single-arm, cohort-based proof-of-feasibility study and is part of the larger BALCoS study. The study team developed the material in six stages.

- Stage 1: The latest publications, evidence-based methods and techniques, and available information regarding a module (for description of modules see Point 3.3; Study Procedures) was consulted, selected, filtered and condensed into module scripts. These scripts outlined all elements of a module (introduction, exercises, psychoeducational content, conclusionary statement) and all members of the interdisciplinary study team were asked to provide feedback. For module 2 (healthy lifestyle), a member of the nutritional counselling team at UHB was asked to review the material. For module 3 (physical activity), the physical therapy team at UHB was asked to collaborate in the development of the script. The first stage concluded with agreement on the content of the module script within the study team and where applicable the expert teams.
- Stage 2: The final scripts were reworked into standardized instructions for digital implementation. The content of the scripts was allocated to the days of the corresponding module (see Figure 2). Pictures and illustrations under the Creative Commons Zero (<https://creativecommons.org/publicdomain/zero/1.0/>) license were used to accompany the written content. The instructions were again reviewed by study team members to ensure correct implementation of the content into digital elements (recordings and edits of interviews, animated videos and audio guides).
- Stage 3: Digital elements were produced, recorded, and edited. Afterwards, they were again reviewed by the team.
- Stage 4: The finished material as well as implementation instructions were uploaded to a cloud-based storage platform for implementation into the smartphone content system

application (provided by DocDok.health; See 7.3 Overview of DocDok System).

- Stage 5: Content implemented by DocDok.health was again reviewed by the study team.
- Stage 6: Content was approved and the final version of each module was uploaded to the smartphone content system application.

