### **6.2 Risk-Benefit Assessment**

The study has strong potential benefits for future PCC patients, hospital staff, and stakeholders by contributing to the knowledge of the pathophysiology of PCC and to a better understanding of risk factors and predictors of PCC. This might also inform treatment options for PCC. A part of the patients included in the cohort study are given the opportunity to participate in the DiLCoS substudy. Participation in the study is not associated with any risks. Completing the neurocognitive testing and the measures of physical performance might be mildly tiring. Having more blood drawn than needed for routine assessment might cause mild discomfort. By participating in the questionnaires or conversations, problem areas can be discussed for the benefit of the patient, which however can also be perceived as unpleasant for a short time. We do not expect any negative effects or damage from routine care. All applied questionnaires are validated, widely accepted, and routinely applied in research and clinical practice. Thus, it can be concluded that the risk-benefit assessment is positive.

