##### ***Risks***

- Additional exposure to information about PCC might increase cognitive load and worrisome thoughts or dispositions.
- Exercises (for example breathing exercises) will be shown how to do correctly, but participants will execute exercises without supervision. Patients are encouraged to execute said exercises in a safe and health-conscious manner and are informed that the exercises might be interrupted at any time should the need arise.

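### The serious-event definition covers only blood sampling and data collection, so a serious event caused solely by the DiLCoS app need not be notified as one, and no rule records it

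*Protocol*

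**What the plan says.** Section 5.3 states the consequence of a serious event: "If a serious event occurs, the research project will be interrupted and the Ethics Committee notified of the circumstances via BASEC within 7 days". The definition is in footnote 1, which belongs to 5.3 although it is printed under 5.7. It has two parts. The causal part requires that it cannot be ruled out that "the event is attributable to the sampling of biological material or the collection of health-related personal data". The seriousness part requires unplanned or prolonged inpatient care, lasting or significant disability, or a life-threatening or fatal outcome. Section 5.3 then gives the expectation: "We do not expect any SAEs to occur as a consequence of the tests administered for this study in addition to standard care". Nothing in section 5 mentions DiLCoS.

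Elsewhere the protocol describes a treatment. Section 2.3 says: "The intervention substudy is designed as a single-arm, cohort-based proof-of-feasibility study". In section 6.2 the general part says "Participation in the study is not associated with any risks". The DiLCoS part of the same section lists risks, including more worrying thoughts from added information about the condition, and the fact that "participants will execute exercises without supervision". Its safety text allows for participants having adverse reactions to the material.

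**The concern.** The causal part of the definition fits a study whose only procedures are tests, blood draws and questionnaires. The rationale in section 1 argues for the lowest-risk category on that basis, because the cohort gives no intervention beyond standard care. DiLCoS was added by amendment (section 2.3). It brings a new possible cause of harm, the app content itself, and the definition does not name it.

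The protocol treats that cause as real. Module 1 deals with post-exertional malaise and tells patients to do only what their energy allows, and Module 3 contains physical exercises. If a participant is admitted to hospital after such an exercise and nothing points to the blood draw or the questionnaires, the stated rule asks for no serious-event notice. What is at stake is patient protection during the substudy, and whether a complete count of such events exists when it ends.

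**Working it through.** No arithmetic applies and the protocol gives no figure to reproduce. The check sets the relevant sections side by side.

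1. **Possible causes of a study-related event.** The protocol describes three: sampling of biological material (3.3, Appendix 2), collection of data including tests and questionnaires (3.3), and the DiLCoS intervention (2.3, 3.3). Footnote 1 names the first two.

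2. **Test case.** Take an event that meets a seriousness criterion and is attributable to an app exercise alone. The seriousness part is met and the causal part is not. The event is not a serious event as defined, so neither consequence in 5.3 follows.

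3. **Is it caught by another rule?** Section 5.2 is the only candidate. Its opening is not limited by cause: it covers any circumstances that endanger participants. Its notices (24 hours to the project leader and sponsor, 7 days to the Ethics Committee) are triggered by having to take protective measures immediately. An event that leads to no such measure triggers no notice.

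4. **Is it recorded anyway?**
   - The DiLCoS safety text in 6.2 tells participants to stop, seek medical advice, contact the team or use emergency numbers. It sets no rule for what staff then record.
   - Appendix 1 has no adverse-event row.
   - The day-6 questions (3.3) are described as feedback on feasibility, comprehensiveness, effectiveness and scope.
   - The chat and telephone contacts in 4.2 are triggered by inactivity and are meant to solve problems. No event log is attached to them.
   - Withdrawal needs no stated reason (3.4), so a participant who stops because of worsening may leave no record of why.

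5. **Was the section adapted to DiLCoS?** Sections 2.1 to 2.3, 3.1 to 3.4, 4.1, 4.2, 6.2, 7.2 and 7.4 each carry a DiLCoS part. No part of section 5 does.

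6. **Consistency within 6.2.** The no-risk sentence comes directly after a sentence offering DiLCoS to part of the cohort. The DiLCoS list of risks follows under its own heading. Read in order, the two do not agree.

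**The case against.** A reader might infer that harm from the app would never be reported. The protocol does not support that. Section 5.2 is open as to cause and reaches the Ethics Committee whenever immediate protective measures are taken. The footnote asks only that attribution cannot be ruled out, so an event of mixed or unclear cause can still qualify. What remains outside is an event attributable to the app alone that prompts no immediate measure.

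A reader might also infer that the substudy would go on to declare the app safe. The protocol plans no such conclusion. The DiLCoS aims and endpoints (2.1, 2.2, 4.1) are effectiveness, feasibility, engagement and satisfaction, and no serious-event rate is planned as a result.

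Nor is deterioration unmeasured. WHODAS, the symptom scales and the fatigue scale are collected at T0, T1, T2 and T3, and change can go in either direction. How worsening is tabulated is commonly left to a statistical analysis plan, which is not shown, so its absence is no fault here.

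The no-risk sentence can be defended as referring to the cohort procedures, since the text after it discusses only testing, blood draws, questionnaires and routine care. That makes it mainly loose wording, but it still needs to be reconciled.

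Finally, the contact channels exist, and the case report form, which is not shown, may capture some complaints. This narrows the gap to a missing rule for recording and notification. It does not close it, because questionnaire scores and feedback on content do not identify serious events or their cause.

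**Conclusion.** The point holds in a limited form. Footnote 1 and 5.3 leave a serious event attributable only to the DiLCoS intervention outside the duty to notify serious events, and the protocol contains no rule to record it. Section 5.2 is a partial safeguard that depends on immediate measures being taken. The protocol's own account of the intervention's risks does not fit a definition that omits the intervention.

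The size of the gap is one of the three study-related causes described. No event rate or sample size enters the argument, and the documents give no basis for estimating how many events would be affected. The conclusion rests on reading the causal part of the footnote as written, and on the assumption that neither the case report form nor a separate procedure contains an adverse-event rule for DiLCoS. If one does, the protocol should refer to it. The change is worth making because it protects participants and costs little.

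**What to change.** Reconcile footnote 1, the statement in 5.3 about tests only, and the no-risk sentence in 6.2 with the DiLCoS safety and risk text. Events possibly attributable to the intervention should fall either within the definition or under a parallel DiLCoS provision. Because 5.3 ties the present definition to HRO Art. 21, the sponsor may find the separate provision easier to place.

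State that such events are recorded when they come to light through the chat, the telephone contacts or the day-6 feedback, with one added feedback item if the form has none. Report their number for everyone who started the app, not only for those in the completer analyses.

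The cost is amendment wording, perhaps one feedback item, and some extra event reports; no visits are added. There is one further consequence. Under 5.3 a serious event also interrupts the project, so a wider definition widens that trigger. The sponsor has to reconcile this when drafting the text.

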## **6 FURTHER ASPECTS**

### **6.1 Overall ethical considerations**

As this study is designed as a registry-based cohort study with a digital intervention substudy, there is little to none potential unethical burden on the participants. This study's conduction will comply with the Declaration of Helsinki (World Medical Association, 2013), the ICH-GCP, and the HRA. Additionally, the EU consortium has dedicated a work package to ethical and privacy considerations and has hired a company to advise and supervise issues regarding data privacy, secure data sharing, ethics of the project, and regulatory compliance within the project. For further justification of the project, refer also to section 1, section 6.2, and the informed consent form.

For ethical considerations regarding the intervention content, refer to section 6.2.

### **6.2 Risk-Benefit Assessment**

The study has strong potential benefits for future PCC patients, hospital staff, and stakeholders by contributing to the knowledge of the pathophysiology of PCC and to a better understanding of risk factors and predictors of PCC. This might also inform treatment options for PCC. A part of the patients included in the cohort study are given the opportunity to participate in the DiLCoS substudy. Participation in the study is not associated with any risks. Completing the neurocognitive testing and the measures of physical performance might be mildly tiring. Having more blood drawn than needed for routine assessment might cause mild discomfort. By participating in the questionnaires or conversations, problem areas can be discussed for the benefit of the patient, which however can also be perceived as unpleasant for a short time. We do not expect any negative effects or damage from routine care. All applied questionnaires are validated, widely accepted, and routinely applied in research and clinical practice. Thus, it can be concluded that the risk-benefit assessment is positive.

#### **DiLCoS Substudy**

##### ***Safety Considerations***

To communicate with the study personell, participants are instructed to use the chat function on the smartphone application. Should the chat function not be available to them due to technical problems, they are informed that they can contact the study team via email. Before any mental or physical exercise, participants are informed that they can stop or interrupt at any time during an exercise should they feel unwell, uncomfortable with the material, experience adverse reactions, or feel negatively impacted in any way by the material provided. They are also advised to seek medical counsel if they feel unable or unsure to execute physical exercises and execute said physical exercise under medical supervision. Participants are instructed that the chat function/study email is not meant for emergency situations. For the unlikely case that an emergency situation arises, participants receive resources in the introduction module with emergency phone numbers, should they feel overwhelmed or negatively impacted by the study material. This is implemented as a safety measure and to ensure that participants engage only in those exercises that are within their capabilities at the time.

##### ***Risks***

- Additional exposure to information about PCC might increase cognitive load and worrisome thoughts or dispositions.
- Exercises (for example breathing exercises) will be shown how to do correctly, but participants will execute exercises without supervision. Patients are encouraged to execute said exercises in a safe and health-conscious manner and are informed that the exercises might be interrupted at any time should the need arise.

## **Benefits**

- Patients receive a 12-week program based on evidence-based treatment recommendations that consider expertise from different specialties (psychosomatics, internal medicine, physical therapy) with access to individual care via chat function on the smartphone application.
- Patients can acquire specific skills and resources to better deal with burdening symptoms and improve their health and well-being.
- Patients can gain a better understanding of disease course and symptoms.

To conclude, given the need for effective interventions for PCC, the risk-benefit assessment is positive.

## **6.3 Rationale for the inclusion of vulnerable participants**

Pregnancy does not affect any study procedures. There will not be any specific risk in relation to pregnancy.

# **7 QUALITY CONTROL AND DATA PROTECTION**

## **7.1 Quality measures**

Data quality is assured through (1) the investigators who are qualified by education, experience, and extensive training (data collection, data entry); (2) continuous monitoring, quality control, and plausibility check of collected data by data managers; (3) internal audit procedures that will guarantee the quality of the findings. Data management will be performed only by authorized and experienced study investigators and project employees.

For quality assurance, the Ethics Committee may visit the research sites. Direct access to the source data and all project-related files and documents will be granted on such occasions.

## **7.2 Data recording and source data**

Data will be collected mainly online via Redcap®, some by paper-pencil (informed consent form, physiotherapeutic assessment) and within the CNSVS program. All collected data and hospital information that is not electronically available will be entered into the study electronic case report form (eCRF) of Redcap®. Data entry will be performed by trained study personnel. Password protection and user-right management ensure that only authorized study investigators, monitors, data managers, and local authorities (if necessary) will have access to the data during and after the study. Back-up of the Redcap® database server will be performed regularly according to established processes by the ICT-department of the UHB. When data gets saved in an eCRF, it will be validated for completeness and discrepancies by a data manager. Clinical data will be retrieved from the patient records and merged in the eCRF with data from Redcap®.

## **DiLCoS Substudy**

Data will be collected via the smartphone application and is only accessible through a secure login on the DocDok digital platform. All collected data will be encoded before any additional analysis. Logins are individualized and password-protected to ensure data safety and traceability of access on the webpage. Data collected from the smartphone application will be hosted in Switzerland (server location and registered seat of partner company Docdok), with some employees of the company working from Israel (safe third country according to EU adequacy decision; registered seat of subsidiary of partner company).

To understand how users interact with the smartphone application, the following data will be collected:

- Frequency of Use: Measuring how often users engage with the application.
- Feature Utilization: Identifying which parts of the application are most frequently used.

- User Engagement Duration: Tracking the amount of time spent on the application during each session.
- Navigation Patterns: Observing how users move through different sections of the application.

This data will be collected using the following methods:

- Automated Tracking Tools: Embedded in the software of the application to track user interactions.
- User Feedback: Questions presented to users for additional qualitative feedback (see Section 3.3 Study Procedures and CRF)

### 7.3 Overview of the DocDok System

To provide the intervention within the DiLCoS substudy, we utilize a delivery platform provided by DocDok.Health. DocDok is a Swiss software company that provides efficient and secure management of digital health content, ensuring a seamless user experience, which has been successfully used in different Swiss healthcare facilities (University Hospital of Zurich (USZ), Lausanne University Hospital (CHUV, Spital STS AG). Their server is located in Switzerland. Data can be downloaded from their server and will then be added to the eCRF of Redcap® by the study personnel.

The DocDok system is a state-of-the-art digital platform that has been specifically tailored for the healthcare sector. It offers a comprehensive suite of features designed to enhance the delivery and management of health-related content on smartphone devices. Key aspects of the DocDok system include:

- System structure: The docdok system is comprised of a smartphone application and web-based access. Users can access the system by login into the application and health care professionals access the system by login into the web-based platform, both with secure logins. This makes the docdok system easily accessible for both user groups.
- Security and Compliance: The system adheres to stringent security protocols, ensuring the confidentiality and integrity of user data. It is compliant with the Swiss Data Protection Law and GDPR standards in Europe, providing a secure framework for handling sensitive health information. Hosting of data is provided in Switzerland.
- User Interface and Experience: DocDok boasts an intuitive and user-friendly interface, facilitating easy navigation and accessibility for users of varying technological proficiency. This enhances user engagement and ensures effective content delivery.
- Customization Capabilities: The system offers extensive customization options, allowing for the tailoring of content and features to meet the specific needs of different user groups, including patients with PCC.
- Real-time Responses: The platform allows responding to user engagement and information provided by the user.
- Support and Maintenance: Ongoing technical support and regular updates are provided to ensure the system remains current with the latest technological advancements and security updates, ensuring uninterrupted service and reliability.
- Engagement and Interaction Dashboard: This dashboard is specifically designed to track and facilitate interactions with patients enrolled in the study. It serves as a dynamic tool for monitoring patient engagement and enabling direct communication. The dashboard provides real-time data on patient interaction with specific content. It thereby acts as interactive communication platform, serving as a two-way communication channel between study personnel and participants. Through this platform, participants can receive personalized messages, reminders, and feedback, while also having the ability to send feedback or queries.

